### Analysis

#### Feasibility and Acceptability

Descriptive statistics will be used to describe recruitment and retention rates and to calculate means on survey items assessing feasibility and acceptability. A benchmark of ≥75% of the *agree* and *strongly agree* (equivalent to an average score of ≥4) responses will be used [83,84]. For the satisfaction and engagement scale, qualitative survey items will be coded by 2 research team members. Interviews will be recorded, transcribed, and uploaded to NVivo (Lumivero) [85] for thematic analysis [86]. The research team will conduct a line-by-line reading of transcripts to identify inductive codes that emerge from the data. The team will then collaborate to develop a codebook that includes operationalized definitions of each of these inductive codes as they apply to the topics addressed in the interviews (ie, feasibility, acceptability, strengths, weaknesses, areas for improvement, and barriers and facilitators to implementation). A study investigator and the research coordinator will code a subset of the data, then convene to resolve discrepancies and revise codes until consensus is achieved on the codebook. Two research team members will then code the entire dataset and meet to achieve consensus on the final codes. The results from these analyses will be used to inform further refinement of the THRIVE protocol before proceeding to a larger randomized controlled trial.

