#### Recruitment

Participants were recruited via referral from clinicians and research coordinators at the 3 recruitment sites, using flyers, email, and verbal communication. Recruitment occurred during each clinic’s operating hours (8:30 AM-5 PM). Recruitment for the pilot trial remained open until at least 60 participants completed the intervention. For the interviews, women who completed either the baseline assessment session only or the full THRIVE intervention were randomly selected and recruited via telephone or email by the research coordinator. Recruitment for interviews remained open until data saturation was achieved, at 12 participants [71].

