##### Feasibility and Acceptability

The data sources are presented in Textbox 1.

Data sources.Recruitment and retention: study logs recorded enrollment, attendance, retention rates, and the percentage of assessments completed.Adherence scales: completed by research team members for 50% of the sessions, these scales assess peer support specialist fidelity to the protocol.Satisfaction and engagement scale: 4 Likert scale survey items from our prior study (eg, “How engaging did you find the program?”) assess satisfaction and engagement.Qualitative feedback: 2 items on the self-report surveys elicited areas for improvement and strengths of the protocol (eg, “What did you like about the program?” and “How could the program be improved?”).Interviews: semistructured interviews assessed program feasibility, acceptability, strengths, and weaknesses (eg, feasibility of attending appointments, acceptability of the study location, satisfaction with the research team, and intervention format and modality). The interviews also assessed alliance with peer support specialists and suggestions for improvement (eg, “How appropriate does the program seem for women who are in substance use treatment?” “How did you feel about your interactions with the peer support specialist who delivered the program?” “What barriers or difficulties did you experience in terms of participating in the study?”).

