## Results

Recruitment, enrollment, and data collection from the 3 sites was completed between June 2024 and March 2025. Of the 92 women recruited and enrolled, 71 (77%) completed the intervention and postintervention assessments, 58 (63%) completed the 1-month follow-up assessments, and 44 (48%) completed the 3-month follow-up assessments. Ten completers, 2 noncompleters, and 2 PSS completed exit interviews. Of the 92 enrolled participants, 45 (50%) were from the Prisma Health Addiction Medicine Center, 42 (47%) from Phoenix Center, and 3 (3%) from Magdalene Clinic. Of the 92 participants, 1 (1%) was American Indian or Alaska Native, 4 (4%) were Black, 1 (1%) were Hispanic, 79 (86%) were White, 2 (2%) identified as multiracial, and 3 (3%) identified as “other.” Racial and ethnic distribution is representative of the patient populations at the recruitment sites. The participants’ mean age was 35 (SD 9.87) years. The most commonly reported substances used included tobacco (79/92, 86%), cannabis (58/92, 63%), alcohol (55/92, 61%), amphetamine-type stimulants (58/92, 63%), and opioids (50/92, 54%; Table 3).

**Table 3 table3:** Types of substances used by enrolled participants (N=92).

Substance types	Participants, n (%)
Tobacco	79 (86)
Alcohol	55 (61)
Cannabis	58 (63)
Opioids (heroin, fentanyl, etc)	50 (54)
Amphetamine-type stimulants	58 (63)
Inhalants	19 (24)
Sedatives	47 (51)
Hallucinogens	32 (35)
Cocaine	44 (48)

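### The acceptability benchmark equates at least 75% agreement with a mean of at least 4, but neither criterion implies the other

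*Protocol article*

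**What the plan says.** In the Analysis section, under Feasibility and Acceptability, the article plans descriptive statistics for recruitment and retention and intends "to calculate means on survey items assessing feasibility and acceptability". The next sentence sets the criterion. It opens with "A benchmark of ≥75% of the", names the two favourable response categories, and closes with a parenthesis saying that this is "equivalent to an average score of ≥4) responses will be used".

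The instrument is described under Measures, Textbox 1, as "4 Likert scale survey items from our prior study". Neither the number of response points nor the scoring is given. The article does not say which statistic decides if the share and the mean disagree.

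On numbers, the Recruitment section says "Recruitment for the pilot trial remained open until at least 60 participants completed the intervention". The Results section reports that, of 92 enrolled, "71 (77%) completed the intervention and postintervention assessments".

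**The concern.** The share of answers in the top two categories counts how many respondents are favourable. The mean also depends on how strongly the favourable ones agree and how unfavourable the others are. Two samples with the same share can therefore have quite different means, and two samples with the same mean can have quite different shares. Calling the two equivalent is a false statement, not a detail left for a fuller document.

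Acceptability is part of the first objective. If the two statistics fall on opposite sides of their cuts, the benchmark as written is both met and missed, and the reader cannot tell which result governs. Data collection is complete, so the choice between them could be made with the answers in view.

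**Working it through.** **Inputs**
- Share criterion: at least 75% agree or strongly agree (Analysis, Feasibility and Acceptability).
- Mean criterion, stated as equivalent: at least 4 (same sentence).
- Respondents: n = 71, the women who completed the postintervention assessments (Results); n = 60, the recruitment minimum (Recruitment). I assume that all of them answered the item.
- Scoring: 1 to 5 with agree = 4 and strongly agree = 5. This is an assumption; a cut of 4 tied to agreement points to it.

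**Thresholds for one item**
- Share rule: 0.75 × 71 = 53.25, so 54 favourable answers are needed (54/71 = 76.1%); 53/71 = 74.6% falls short. For n = 60, 0.75 × 60 = 45.
- Mean rule: the scores must sum to at least 4 × 71 = 284, or 4 × 60 = 240.

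**Does the share imply the mean?** With exactly 54 of 71 favourable, the mean can lie anywhere between
- (54 × 4 + 17 × 1)/71 = 233/71 = 3.28, and
- (54 × 5 + 17 × 3)/71 = 321/71 = 4.52.

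A moderate pattern is enough to split the rules. With 54 at 4 and 17 at 3 the mean is 267/71 = 3.76, so the share passes and the mean fails. Even 70 at 4 and one at 3 (98.6% agreement) gives 283/71 = 3.99. For n = 60, 45 at 4 and 15 at 3 gives 75.0% and 225/60 = 3.75.

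**Does the mean imply the share?** The smallest share compatible with a mean of 4 has favourable answers at 5 and the rest at 3. Solving 5p + 3(1 − p) ≥ 4 gives p ≥ 0.50. For n = 71, 36 at 5 and 35 at 3 gives 285/71 = 4.01 with 36/71 = 50.7% agreement, so the mean passes and the share fails. For n = 60, 30 at 5 and 30 at 3 gives 240/60 = 4.00 with 50.0%.

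**How common are splits?** Listing every possible set of response counts for n = 71, 38,475 sets pass both rules, 29,070 pass only the share rule and 20,826 pass only the mean rule. These are counts of patterns, not probabilities.

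**Other scorings.** Other instruments in Textbox 2 imply 4-point items (52/13 = 4) and 7-point items (140/20 = 7), so I checked those lengths too.
- Scored 1 to 4, a mean of 4 requires every answer to be the top one, which 75% agreement does not.
- Scored 1 to 7 with the top two options at 6 and 7, 75% agreement forces a mean of at least 0.75 × 6 + 0.25 × 1 = 4.75. However, a mean of 4 is also reached when everyone answers 4, with 0% agreement.

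The equivalence fails for each.

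**Precision.** At the passing count of 54/71, the Wilson 95% interval for the share is about 65% to 84%.

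**The case against.** **The parenthesis may define agreement.** It sits between the response categories and the word responses. It could mean only that agreement is a score of 4 or more, or a participant's average of 4 or more over the four items, with 75% as the sole threshold. That reading is possible, but the word average and the planned item means speak against the first form. The second form is not an equivalence either: answers 5, 5, 3, 3 average 4.0 with half the items agreed, while 4, 4, 4, 3 average 3.75 with 75% agreed. If several readings are tenable, the benchmark is not fixed.

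**The stakes are modest.** This stands. No test, error rate or formal go/no-go rule hangs on the benchmark. The results are to inform refinement of the program, and interviews and open-ended items also bear on acceptability. A mean of 4 with about half favourable is a boundary case that needs nobody to disagree.

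**Stronger readings that the article does not support:**
- A reader might infer that this is the plan's only numeric threshold. It is not: the Intervention section has a screening cut of 3 or more for referral, and recruitment had a minimum of 60 completers. It is the only numeric acceptability benchmark.
- A reader might infer from the sample item, which asks how engaging the program was, that agree/disagree categories do not fit the scale. One example stem, with the response options not shown, cannot establish that.
- A reader might infer that the share should be taken over all 92 enrolled. That is a separate preference. It would count women who did not answer as unfavourable, and retention is already reported on its own.

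**Conclusion.** The stated equivalence is wrong. Under 1-to-5 scoring with agree = 4 it fails in both directions: at n = 71 the share rule can be met with a mean of 3.76, and the mean rule can be met with 50.7% agreement. The conclusion does not depend on 71 being the exact number of respondents, since the same splits occur at 60. It also survives the 4-point and 7-point scorings, although on 7 points only one direction fails.

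The consequence is moderate. A first-objective result could be reported as meeting or missing its benchmark depending on which statistic is used. It remains a descriptive criterion for program refinement, and nothing in the article shows that the choice has been exploited.

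**What to change.** Delete the statement of equivalence. Name one deciding criterion: at least 75% of responses in the top two options, which is the article's main clause; for an item answered by 71 women this means 54 favourable answers. State the response scale, the scoring and which options count as favourable. Give the share with a 95% confidence interval and report the mean as a descriptive statistic.

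Because data collection ended in March 2025, label this as a clarification made after data collection. Report both statistics, so that readers can see whether the choice changes the conclusion.

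The cost is a sentence or two and no new data. The one downside is that a result passing only on the mean would no longer meet the benchmark; conversely, a result with a sufficient share but a mean below 4 would clearly meet it.

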#### Preliminary Effectiveness

##### Analytic Sample

The primary analytic sample will include all participants who completed the baseline survey; this will serve as the intention-to-treat sample. We will also conduct modified intention-to-treat analyses including only participants who attended 1 THRIVE session.

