### Intervention

The intervention consists of two 60-minute sessions delivered in-person by PSSs in either group or individual format. Groups consist of 5 to 10 individuals. The sessions include a combination of information; interactive exercises to fuel discussion on knowledge, attitudes, and behaviors; and skills-building activities. Handouts accompany each session with key takeaways and resources. Topics include (1) definitions of SV and IPV, (2) consent, (3) healthy versus unhealthy relationships, (4) help seeking and resources for trauma-related care, (5) protective behavioral strategies, (6) safe dating, (7) alcohol and drug safety (8) sexual assertiveness, (9) overcoming barriers to protective strategies, and (10) creating a behavior change plan. Table 1 presents the intervention content. In addition to the prevention education program, PSSs screen each participant for PTSD using the Primary Care PTSD Screen for DSM-5 (PC-PTSD-5) [69]. Participants who score ≥3 (indicating a potential PTSD diagnosis) are referred to local mental health providers who provide trauma-informed care. If participants are already enrolled in mental health care, the PSS ensure that the provider is informed of the participant’s PTSD symptoms.

**Table 1 table1:** The Healthy Relationships and Interpersonal Violence Education program content.

Sessions and topics			Content		Outcome measures		Information, motivation, behavioral skills model components

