### Participants and Procedure

#### Participants

We recruited and enrolled 92 women (71 completers) in substance use treatment for a single-arm trial of THRIVE. The inclusion criteria include (1) adults (aged ≥18 y), (2) identifying as women, (3) currently enrolled in substance use treatment (behavioral or pharmacological), and (4) willing to accept random assignment to a waitlist (usual care) or THRIVE. The exclusion criteria include (1) having a severe medical or psychiatric disability that could impair ability to perform study-related activities (determined by their substance use treatment provider), (2) unable to independently read and comprehend the consent form or other study materials, and (3) unable to read and speak English. A total of 10 to 20 women as well as the 2 PSSs were selected to complete exit interviews. The inclusion criteria for the interviews included (1) women who completed either the baseline survey only (intervention noncompleters) or the full THRIVE intervention (intervention completers); and (2) for the PSSs, those who delivered the THRIVE intervention.

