#### Retention Plan

Beyond the incentive structure for study participation, implemented additional strategies to ensure high retention rates. First, we asked for ≥2 alternate contacts at baseline so that we could continue to reach participants during follow-up. Written consent was also obtained to contact other persons for locating the participant for follow-up. The research coordinator contacted all participants at least once between follow-up assessments to maintain a connection and updated contact information. Participants received at least 3 email or SMS text message reminders to complete surveys. The research coordinator made at least 20 attempts to contact participants who did not respond or complete assessments before considering them lost to follow-up. The research coordinator attempted to make regular contact with participants to collect data at each assessment interval, regardless of whether they attended the intervention. The research coordinator also worked with health care providers to determine when eligible participants had appointments to better facilitate scheduling assessment sessions around already scheduled health care appointment times.

Research team members attended staff meetings at each recruitment site to update the sites on enrollment and retention status and to work with the sites on overcoming barriers to recruitment and retention. A member of the research team was present on site throughout active recruiting periods to connect with health care providers, screen eligible participants, and meet with potential participants around the time of their health care appointments.

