##### Missing Data

Every effort was made to minimize missing primary outcome data. However, the primary analytic strategy relies on mixed effects models, which is unbiased under missing-at-random assumptions and is the most frequently accepted approach in longitudinal data analysis [87]. Characteristics of patients who are lost to follow-up will be compared to those who complete the study to assess the degree of any selection bias due to attrition. We will complete a sensitivity analysis to compute indices of sensitivity to the nonignorability of missing data. If these analyses indicate evidence that nonignorability will impact model parameter estimation, we will apply fully conditional specification multiple imputation methods, which are applicable to nonignorable missing data [87,88].

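### At the postintervention wave the intention-to-treat model appears to predict the change of 21 of 92 women from completers, with no alternative estimate fixed, and the modified set is misworded

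*Protocol article*

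**What the plan says.** All places are in the protocol article.

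- **Analytic Sample.** The primary set: "The primary analytic sample will include all participants who completed the baseline survey; this will serve as the intention-to-treat sample". The second set: "We will also conduct modified intention-to-treat analyses including only participants who attended 1 THRIVE session".
- **Intervention.** "The intervention consists of two 60-minute sessions delivered in-person by PSSs in either group or individual format".
- **Results.** Of 92 women enrolled, "71 (77%) completed the intervention and postintervention assessments". The Abstract gives the same 71 for completing the intervention alone. The 1-month and 3-month counts are 58 and 44.
- **Participants.** The exit-interview criteria cover "women who completed either the baseline survey only (intervention noncompleters") or the full programme.
- **Assessment Plan.** Baseline and postintervention surveys were collected in person on a tablet, around the THRIVE sessions. The 1-month and 3-month surveys went out by text message or email.
- **Retention Plan.** Data were sought at each interval "regardless of whether they attended the intervention".
- **Missing Data.** The primary strategy rests on "mixed effects models, which is unbiased under missing-at-random assumptions". The section adds a comparison of women lost to follow-up with those who complete, nonignorability indices and, if these point to a problem, fully conditional specification multiple imputation.

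**The concern.** An intention-to-treat label tells the reader that the estimate applies to every woman with a baseline survey. At the postintervention wave, having an outcome seems to coincide with having completed the programme. There is no control arm to show how women change without it. The model can therefore learn about change at that wave only from women who received the full programme, and it carries that change over to those who did not. Missing at random is hard to defend when missingness is tied this closely to not completing the intervention.

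The modified set does not help. Read literally, it keeps women with one session and leaves out those with two. Read as at least one session, it holds nearly the same postintervention data as the primary set, so agreement between the two would reassure wrongly. What is at stake is the effect size carried into the randomised trial that the article says these findings will help design.

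**Working it through.** **1. The article's own figures.** 71/92 = 77.2%, 58/92 = 63.0% and 44/92 = 47.8%, matching the stated 77%, 63% and 48%. Not completed: 92 − 71 = 21, and 21/92 = 22.8%.

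**2. Do the 21 have postintervention data?** Three places point the same way: one count of 71 for both intervention and assessment (Abstract, Results); in-person collection around the sessions (Assessment Plan); and noncompleters described as having the baseline survey only (Participants). This is an inference, but a consistent one. It does not extend to 1 and 3 months, where surveys were online and non-attenders were also contacted.

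**3. Dilution.** Let d be the completers' change and k the fraction of d that noncompleters experience. The all-enrolled change is d × (71 + 21k)/92. With alike baselines the model returns about d, so the ratio of estimate to all-enrolled change is 92/(71 + 21k).

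| k (assumed) | Ratio |
|---|---|
| 0 | 92/71 = 1.30 |
| 0.5 | 92/81.5 = 1.13 |
| 1 | 92/92 = 1.00 |

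At k = 0 the all-enrolled change is 71/92 = 0.77 of d, or about 23% smaller. The site counts in Results sum to 45 + 42 + 3 = 90. On a base of 90 the k = 0 ratio is 90/71 = 1.27.

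**4. Baseline differences.** Under a random-intercept model with intraclass correlation ρ and baseline in the outcome vector, suppose noncompleters start s SD further in the direction of change. The estimated change is then approximately d − (1 − ρ) × (21/92) × s. With d = 0.5 SD:

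- s = +0.5: 0.5 − 0.7 × 0.228 × 0.5 = 0.42 at ρ = 0.3, and 0.5 − 0.3 × 0.228 × 0.5 = 0.47 at ρ = 0.7.
- s = −0.5: 0.58 at ρ = 0.3 and 0.53 at ρ = 0.7.

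**5. Simulation.** A random-intercept mixed model was fitted by restricted maximum likelihood, with 60 replicates per scenario. The numbers observed were 92, 71, 58 and 44 at the four waves. Completers changed by 0.5 SD, noncompleters by 0 and with no later data (all assumed). The true all-92 change is 0.5 × 71/92 = 0.386 SD. Postintervention estimates in SD:

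| Noncompleter baseline shift | All 92 (ρ = 0.3, 0.5, 0.7) | Completers only |
|---|---|---|
| 0 | 0.519, 0.485, 0.510 | 0.523, 0.480, 0.509 |
| +0.5 SD | 0.416, 0.448, 0.468 | 0.509, 0.506, 0.499 |
| −0.5 SD | 0.575, 0.557, 0.536 | 0.496, 0.495, 0.501 |

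With equal baselines the two analyses are practically identical. With unequal baselines they part, as step 4 predicts. Every all-92 value exceeds 0.386, with ratios from 0.416/0.386 = 1.08 to 0.575/0.386 = 1.49.

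**6. Does the planned fallback give a different answer?** The indices measure how sensitive an estimate is; they do not supply another estimate. Fully conditional specification draws missing values from models fitted to observed women. Without a stated shift or a no-change rule it again assumes missing at random, and at this wave the observed women are the completers.

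**The case against.** Keeping every woman with a baseline survey in a missing-at-random mixed model is conventional, and the article does not rest on that alone, since Missing Data plans an attrition comparison, nonignorability indices and conditional imputation. The article also concedes that a single-arm trial cannot test efficacy rigorously. All of this stands. The planned steps are real safeguards, but as written none of them produces an estimate under a different assumption about noncompleters.

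A reader might go further and infer that the whole intention-to-treat analysis is a completers' analysis. The documents do not support that. The baseline-only description is an eligibility rule for exit interviews, the follow-up surveys were online, non-attenders were pursued, and nothing says that the 58 and 44 responders all come from the 71. Nor does the model simply hand noncompleters the completers' change, because it conditions on their baseline and covariates.

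A reader might also take the 30% excess as a known bias. It is a scenario. Some of the 21 may have attended one session, all were enrolled in substance use treatment, and no figure in the article says that they stayed unchanged.

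Finally, the literal reading of the modified set is unlikely to be what was meant. That is so, but the wording still needs correcting.

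**Conclusion.** The point holds for the postintervention wave. The 21 of 92 women who did not complete appear to have no outcome there, so the estimate labelled intention-to-treat predicts their change from completers. The overstatement relative to the all-enrolled change is about 1.30-fold if noncompleters did not change and 1.13-fold if they changed half as much, both assuming alike baselines. With no change and a baseline difference of 0.5 SD either way, the simulated ratios ran from 1.08 to 1.49. If noncompleters changed as much as completers and baselines are alike, there is no overstatement.

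For 1 and 3 months no size can be given until the number of noncompleters who responded is known. Dividing 92 by 58 or 44 would also treat completers lost later as unchanged, which nothing in the article supports. The wording of the modified set is a separate, plain error of drafting in a two-session programme.

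**What to change.** 1. Keep the mixed model on all women with a baseline survey as the primary analysis.
2. Report, for each wave, how many completers and how many noncompleters gave data.
3. In Missing Data, replace the unspecified, conditional fallback with a sensitivity analysis that is always run. It imputes no change from baseline for noncompleters without follow-up data (baseline-mean multiple imputation) and is reported beside the primary estimate. Describe it as one stated departure from missing at random, not as the true value.
4. In Analytic Sample, change "including only participants who attended 1 THRIVE session" so that the modified set requires attendance at *at least one* session.

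The cost is a few lines of text and one extra imputation run. The all-enrolled effect shown beside the primary one may be smaller, by up to about 23% (21/92) at the postintervention wave when baselines are alike.
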